### Ethics

The study is being conducted in Compliance with the Declaration of Helsinki [52]. Approval was obtained from the Ethics Committee of the State Chamber of Physicians in Hamburg, Germany (reference number: PV4802).

## Discussion

The aim of this randomized-controlled trial will be to evaluate the effectiveness of a newly developed German Internet intervention, named *Vorvida,* which aims to help adults reduce their problematic alcohol consumption. *Vorvida* is, to our knowledge, the first dialogue-based Internet intervention for alcohol consumption reduction that uses an extensive tailoring approach to convey CBT content to users. Studies on a similar designed Internet self-help program for depression, named *Deprexis,* showed consistently good effectiveness, replicated in six RCTs to date [26, 53–56]. Moreover, *Vorvida* uses a fully responsive web-design approach, permitting users to switch between different devices, including smartphones, while continuing within the program wherever they left off on another device. We anticipate that the increased flexibility afforded by these technological features will translate into higher effectiveness compared to less flexible interventions that have been studied in other trials. This study is of particular interest because there is still a lack of RCTs on the effectiveness of extended and tailored Internet interventions for adults with harmful drinking or alcohol dependence [16].

There are also some limitations that ought to be considered. First, our study will only include problem drinkers with Internet access and moderate Internet literacy who are willing to participate and be randomized to a study condition. This will result in a sample bias in the sense that the sample cannot be expected to be representative of the general population of all problem drinkers, regardless of their Internet affinity or ability to use computer programs. However, the intended audiences for this intervention are clearly adults who are motivated and able to engage with Internet programs; therefore, the sample can be expected to be representative of the relevant population. In short, the results of this trial might suggest that *Vorvida* is effective for problem drinkers who can and wish to use Internet programs, although it will not inform the question of whether the program would also be effective for all persons with problematic drinking patterns, including those who cannot or do not want to use Internet-based programs.

It should also be noted as a limitation that Internet-based studies often suffer from high attrition, the “phenomenon of participants dropping out of eHealth trials” [57]. Efforts are made here to reduce attrition, though, as participants receive a gift voucher if they fill out all questionnaires from t1 to t2.

An additional limitation is that there will be no face-to-face diagnostic interviews administered by a qualified professional. Interested persons will be included or excluded based on their self-reported screening questionnaire filled in online. This limitation is explained primarily by limited resources, although it is also possible that initial face-to-face contacts can actually boost the effects achieved by Internet interventions, complicating the interpretability of such trials [27, 54].

Another limitation is that only self-report measures will be used, which introduces potential biases inherent in self-report questionnaires, such as social desirability. However, previous studies suggest that self-assessed methods in alcohol research tend to be reliable and valid [58, 59]. However, we acknowledge that the validity of the outcome measures used here has not explicitly been tested for online settings. Finally, a limitation is that we do not ask participants to provide open feedback about the program, but we do ask for the intervention groups’ satisfaction with *Vorvida*, using validated questionnaires.

In addition to these methodological limitations, it is important to note how potential suicidality among participants will be addressed. If suicidal tendencies are detected (e.g., because participants select relevant questionnaire responses), we will exclude the respective person from the study. Support numbers and contact addresses will be provided only through our study website. The only personal contact with a participant will occur if a participant will call the research investigators concerning any questions about the study procedure.

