### Study procedure

We developed a study website (www.vorvida-studie.de) to inform potential participants about the aim of the study, the procedure, data protection and possible benefits and risks of the study. Participants will be informed that they can withdraw from the study at any time without having to disclose reasons. After reading all information, electronic informed consent will be sought before the screening for eligibility. Persons willing to participate will be asked to fill out an online screening questionnaire to test if they meet inclusion criteria. Within one week, participants will receive an e-mail to inform them whether inclusion criteria are met and, if so, what next steps are required. All included participants will receive a link to the online baseline questionnaire (t0) and are asked to respond to it within one week. An e-mail reminder will be sent out after two and after four weeks to those who did not reply. After responding to the baseline questionnaire, participants will be randomized to one of the two study arms. Each participant will receive an e-mail with the randomization result. The e-mail of the participants randomized to the *Vorvida* group will contain the access key to the *Vorvida* program, a 12 digit number registration number that activates the program for 180 days after initial registration. The CAU/WL group will be informed about the waiting time of six months until they receive their access key to the program.

Three (t1) and six months (t2) after completing the baseline questionnaire (t0), participants in both groups will receive an online-link for the follow-up questionnaires. They will be asked again to respond within one week and will receive two reminder e-mails, after two and after four weeks, if they do not do so. Furthermore, participants in the *Vorvida* group will receive an e-mail reminder to encourage program use after three weeks, six weeks, nine weeks and sixteen weeks after receiving the access key.

A bias of attrition, meaning the loss of participants to the follow-up assessment is a well-known problem in RCTs, particularly of Internet interventions, and can affect the strength of the findings [28]. Because non-monetary incentives have been shown to reduce attrition in online trials [29, 30] each participant who completes the baseline questionnaire (t0) and the two follow-up questionnaires (t1 and t2) will receive a 10€ Amazon gift voucher.

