### Sample size

The sample size is estimated using Gpower v.3.0.5 software [32]. The calculation is based on the primary outcome measure (alcohol consumption).

Other studies on Internet self-help programs on alcohol misuse showed mainly small effect sizes between d > .2 and d < 0.4 [11, 18].

To detect effect sizes of d = 0.28, an effect derived from a meta-analysis of self-guided Internet interventions [18], with a power of 0.80 and a significance level of 0.05 to compare the *Vorvida* group with the CAU/WL group, a target sample size of N = 404 (n = 202 per group) is required. Since it is expected that 20 % of variance can be explained through baseline-covariance, adjusted effect sizes were used in this power calculation.

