### Assessments

We will conduct a total of three assessments. The first will be the baseline assessment (t0) before the randomization and the start of the intervention. The second and primary outcome will be three months after the randomization and the start of the intervention (t1) and the third will be after six months when the intervention is completed (t2) (see Table 2). All assessments will be conducted as self-reports via online-questionnaires, using a secure and widely used external online survey collection service (www.surveymonkey.com). The links to the questionnaires will be e-mailed to the participants.

**Table 2 Tab2:** Measures and measurement points

	AUDIT-C	QFI^1^	TFB^2^	Being Drunk^3^	Binge Drinking^3^	CAEQ^4^	AASE-G^5^	RCQ-G^6^	Readiness-Ruler^7^	ZUF-8^8,9^
Screening	X	X								
t0 baseline		X	X	X	X	X	X	X	X	
t1 three month follow-up		X	X	X	X	X	X	X	X	X
t2 six month follow-up		X	X	X	X	X	X	X	X	X

^1^Quantity- Frequency-Index (amount of alcohol in g) last 30 days, ^2^Timeline-Follow-Back (amount of alcohol in g) last 7 days, ^3^Single item, ^4^ The Comprehensive Alcohol Expectancy Questionnaire, ^5^Alcohol Abstinence Self-efficacy Questionnaire, ^6^Readiness to change Questionnaire, Readiness-Ruler, ^8^Patient satisfaction questionnaire, ^9^Intervention group only

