### Trial status

Currently recruiting (N_current_ = 340 as of December 15^th^).

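### Detected suicidality leads to exclusion, but the support contacts stay on the study website and nothing as written puts them in front of the person at disclosure or exclusion

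*Protocol article*

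**What the plan says.** Inclusion and exclusion criteria (text and Table 1) make suicidal ideation or tendency a reason for exclusion.

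The last paragraph of the Discussion sets out how suicidality will be handled, in three statements:

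- Action: "If suicidal tendencies are detected (e.g., because participants select relevant questionnaire responses), we will exclude the respective person from the study".
- Support: "Support numbers and contact addresses will be provided only through our study website".
- Contact: "The only personal contact with a participant will occur if a participant will call the research investigators concerning any questions about the study procedure".

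The surrounding procedure is described elsewhere. Under Recruitment and Study procedure, potential participants visit the study website, read the information there, give electronic consent and then complete an online screening questionnaire. The result follows by e-mail: "Within one week, participants will receive an e-mail to inform them whether inclusion criteria are met and, if so, what next steps are required". Under Assessments, the three assessments (t0, t1, t2) are completed "using a secure and widely used external online survey collection service", and "The links to the questionnaires will be e-mailed to the participants".

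**The concern.** The trial asks problem drinkers, including people with alcohol dependence, something that can reveal suicidality, and it acts on the answer by excluding the person. It already holds a list of support contacts. The stated rule places that list in one location and does not connect it to the two moments when it matters most: when the response is given, and when the person is told that they cannot take part.

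The stake is participant safety. Followed as written, the rule lets the study learn that someone may be at risk and end that person's participation, while leaving the person to return to a website to find help. The same paragraph provides no staff outreach that would fill the gap, so the way the list is presented carries more weight.

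**Working it through.** No arithmetic applies. The check sets the relevant sections side by side and follows a person through each stage at which suicidality could come to light.

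**1. Before screening.** Recruitment and Study procedure route people through the study website before consent. The Discussion says the support contacts are provided through that site. A person may therefore have been able to see them before answering any question. The Study procedure's own account of the site mentions aim, procedure, data protection, benefits and risks, and does not mention support contacts. Since the Discussion does, this is no contradiction.

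**2. At screening.** Suicidality is an exclusion criterion, and the Discussion says that people are included or excluded on the self-reported screening questionnaire. This is the main point of detection. The document does not say which item detects suicidality: Table 2 lists only AUDIT-C and QFI at screening. Nor does it say where the screening form is hosted. If the form sits on the study website, the distance to the contacts is small. In either case, no display or link triggered by the response is described.

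**3. At notification of exclusion.** The eligibility e-mail arrives within one week. Its described content is whether the criteria are met and, for those who meet them, the next steps. Its full wording is not given, and support contacts are not mentioned.

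**4. At t0, t1 or t2.** The Discussion's reference to questionnaire responses leaves later detection possible. These questionnaires run on an external service reached by e-mailed link, so a respondent need not pass through the study website. Table 2 lists no suicidality item at these visits, so whether detection would occur there is not established.

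| Stage | Website on the described route? | Contacts described as shown or sent at that moment? |
|---|---|---|
| Before consent | Yes | Available on the site |
| Screening response | Not stated | No |
| Eligibility e-mail | No | No |
| t0 to t2 response | No | No (and no suicidality item listed) |

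**Result.** At every stage after consent, the person has to go and find the list. The Discussion describes no other route.

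**The case against.** Four points can be made on the other side.

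*The route to screening runs through the website.* This is correct and narrows the harm: a reader might infer that people are screened without ever having had access to support contacts, and the documents do not support that. But having passed through a site before consent is not the same as being shown the contacts on disclosing, or on being told of exclusion up to a week later.

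*The external survey service covers a different stage.* This is also correct. The separation from the website is documented for t0 to t2, where no detecting item is listed, and not for screening. A reader might infer that suicidality is measured at follow-up and disclosed off-site. The document does not establish that, so this argument is limited to possible later detection.

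*The word 'only' may just rule out staff outreach.* The sentence that follows it concerns personal contact, so this reading is plausible. A link to the website in an e-mail or on a survey page would also fit the present wording. It would therefore be too strong to say that the rule forbids every form of active signposting. What stands is that the wording can be read as making the website the sole and passive channel. If the intention was only to exclude outreach, the sentence should say so.

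*Screen logic and e-mail text belong in the full protocol, and ethics approval was obtained.* An article's silence on such details would be no finding. Here, though, the article states a rule and limits it, and the rule can be improved as stated. Ethics approval neither shows that the contacts are delivered at disclosure nor stands in the way of adding this.

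**Conclusion.** The point holds as a low-cost safety improvement. The stated procedure excludes the person, keeps the support contacts on the study website and leaves personal contact to the participant's initiative. Nothing as written brings the contacts to the person at disclosure or exclusion.

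Its size cannot be put as a number of people: the document gives neither a disclosure rate nor the number screened, and the conclusion depends on neither. It rests on two assumptions: that the Discussion paragraph is the operative rule, and that the eligibility e-mail and questionnaires contain no support contacts beyond what is described.

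A reader might infer that the trial offers no support to people at risk. The documents do not support that: contacts are provided, and the CAU/WL section leaves participants in both arms free to seek any other help. Nor is this a statistical defect. Sample size, power, alpha and the planned analyses are untouched.

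**What to change.** Replace the sentence on support contacts with wording such as:

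> Support contacts are listed on the study website, are shown or linked automatically when a relevant response is selected, and are included in any e-mail telling a person of exclusion. Study staff make no personal outreach.

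This removes the ambiguity of 'only' and keeps the restriction on staff contact that the authors may have intended. It changes only where and when an existing list is presented.

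The cost is one conditional survey page or link, one paragraph in an e-mail that is already sent, and a minor amendment. It needs no additional staff or risk assessment and leaves eligibility, outcomes and analysis unchanged. Trial status reports that recruitment was still open, with 340 recruited, against the target of 404 given under Sample size. The change could therefore still reach people yet to be screened, and anyone in whom suicidality is detected later.

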## Conclusions

If the results from this trial show effectiveness for the Vorvida program, this would suggest that this Internet intervention could be recommended for adults who seek help to overcome problematic drinking. This would not mean, though, that the program could serve as an alternative to established treatments, as such a comparison is not part or purpose of this trial. If shown to be effective, the Internet-based program *Vorvida* could be widely implemented to increase the accessibility of helpful techniques for problem drinkers who desire such help. It could be implemented in outpatient settings (e.g. general practitioners offices, treatment centers, welfare organizations) or inpatient settings. If the effects of this intervention will be found to be of a magnitude that is clinically relevant or relevant from a public health (population-based) perspective, this intervention could be used to reduce the existing treatment gap for alcohol-related disorders and thereby improve the quality of care for those affected by alcohol misuse.

### Trial status

Currently recruiting (N_current_ = 340 as of December 15^th^).
